### Human Research Ethics Committee approval

The current study has received approval from the Parenting Research Centre’s Human Research Ethics Committee (HREC; 17/12/2012). Any modifications to the study protocol which may impact on the conduct of the study, potential benefits of the participants or may affect their safety, including changes of study objectives, study design, participant population, sample sizes, study procedures, or significant administrative aspects will require a formal amendment approved by the principal investigators and HREC.

## Discussion

*Cry Baby* is the first randomised, controlled, superiority trial to examine whether evidence based advice on managing infant sleep and crying can be effectively delivered online. This trial will establish whether involvement from a health professional and/or weekly email prompts are necessary to engage parents of newborns with online programs, and additionally, provide insight in to the demographic characteristics of parents who choose to access advice online. Our findings will inform the development, design and retention strategies of other trials of online programs.

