**Methods/Design:**

This study is a randomised, parallel group, superiority trial, with all participating primary carers of infants aged 2 to 12 weeks, receiving access to the online program. Two modes of recruitment will be compared: recruitment via an online notice published on a non-commercial, highly credible and evidence-based website for parents and carers and via the parent’s Maternal and Child Health nurse. After baseline assessment, parents will be randomised to one of two support conditions: online program alone or online program plus weekly email prompts. Follow up data will be collected at 4 months of infant age.

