### Study setting and recruitment

Participants will be primary carers of infants aged 2 to 12 weeks, recruited by one of two recruitment modalities: advertising on the Raising Children Network (www.raisingchildren.net.au), or recommendation from their MCH nurse. The Raising Children Network website is a non-commercial, evidence-based, quality assured, government-funded online resource that covers a broad range of parenting topics and had over 5.7 million visits in the 2013 calendar year (personal communication). A notice will be placed on relevant pages on the Raising Children Network, as well as its social media (e.g., Facebook, Twitter). This notice will contain a link to the study website where parents can gain more information and take part in the program if desired.

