Recruiting some of our sample from Australian wide online advertising and some from a specific region, introduces systematic differences to the groups. In an attempt to reduce this as much as possible, we selected the Melbourne (state of Victoria, Australia) Local Government Area (LGA) of the City of Yarra for MCH nurse recruitment, due to both its high birth rate per annum [45], and broad cultural and socioeconomic diversity [46]. All MCH nurses within this LGA (11) will invite parents of infants attending the 2 week appointment to participate in the trial. The 2 week appointment will be specifically targeted as it was suggested by the nurses that this appointment is less intensive than the in-home appointment at 7–10 days postpartum, and it is unusual for parents of infants aged less than 2 weeks to request information on infant sleep and crying so soon after birth. Recruitment will run for a 12 week period and will allow for later determination of the percentage of parents in the general community that are likely to take part in an online program if suggested by their MCH nurse (birth rate data for this region, throughout this time period will be compared to our sample). MCH nurses will provide parents with a postcard, inviting them to participate in the program. The postcard will contain brief information about the study and a link to the study website so they can gain further information about the research. Participants who indicate that they heard about the Cry Baby program via their nurse *and* via online advertising will be classified as having been recruited via their nurse since it is the effect of encouragement from a health professional that we aim to examine. The Cry Baby program is currently only available to those willing to take part in the research trial and has not been broadly advertised outside the Raising Children Network. This means it is very unlikely that parents would have the program suggested to them by other health professionals.

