### Statistical methods

A range of descriptive and multivariate data analyses will be used to assess the aims of the study. Descriptive statistics (e.g., Chi-square for categorical variables; means and standard deviations for continuous variables) will be presented for the sample demographics, number of times participants access the program, and proportion of participants completing the program. Demographic characteristics of the sample will be compared to country-wide averages obtained from the most recent Australian Census data. Characteristics of infants taking part in the research will be compared to MCH data for babies born within the same geographic area at the time of study recruitment. A mixed-design analysis of variance (split-plot ANOVA) will be conducted to compare the intervention conditions (between-subjects factor) on each of the continuous outcomes at follow-up (within-subjects factor). Effect sizes will be reported where appropriate, with 0.01, 0.06 and 0.14 as small, medium and large effect sizes for multivariate η2, while 0.2, 0.5 and 0.8 are small, medium, and large effect sizes for Cohen’s *d*. All analyses will control for child age given that time of enrolment varied between 2 and 12 weeks postpartum. Finally, intention-to-treat analysis will be conducted using Full Information Maximum Likelihood for missing follow-up data.

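### Nurse versus website recruitment is a non-randomised comparison with child age as its only named adjustment, yet the Discussion promises to establish whether professional involvement is necessary

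*Protocol article*

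**What the plan says.** Randomisation covers one factor (Abstract, Methods/Design): "After baseline assessment, parents will be randomised to one of two support conditions: online program alone or online program plus weekly email prompts". The other factor is how the parent arrived. Participants are "recruited by one of two recruitment modalities: advertising on the Raising Children Network (www.raisingchildren.net.au), or recommendation from their MCH nurse" (Study setting and recruitment). Parents who learned of the study from a nurse and also "via online advertising will be classified as having been recruited via their nurse"; the stated reason is an interest in what professional encouragement does.

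The same section is candid about the consequence: "Recruiting some of our sample from Australian wide online advertising and some from a specific region, introduces systematic differences to the groups". The mitigation it describes is the choice of one Melbourne local government area with a high birth rate and a diverse population.

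Study objectives (second objective) asks whether nurse-recommended parents are more likely to complete the program and to use its strategies. Outcome measures plans to compare the primary outcome across recruitment mode as well as across trial arms. Statistical methods then gives one control: "All analyses will control for child age given that time of enrolment varied between 2 and 12 weeks postpartum". Its analysis of variance has intervention condition as the between-subjects factor; recruitment mode is not mentioned there.

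The Discussion draws the conclusion in advance: "This trial will establish whether involvement from a health professional and/or weekly email prompts are necessary to engage parents of newborns with online programs". The Abstract is milder and says that results will indicate this, but it also speaks of necessity. The Discussion further describes the trial as the first "to examine whether evidence based advice on managing infant sleep and crying can be effectively delivered online".

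**The concern.** The Discussion puts a randomised question (emails) and a non-randomised one (nurse involvement) in a single sentence and promises the same strength of conclusion for both. The nurse group comes from one locality and is invited at the 2-week check. The website group is drawn from the whole country, found the notice itself, and may have infants up to 12 weeks old. The groups can therefore differ in region, socioeconomic position, infant age and reason for taking part, and each of these could influence completion and strategy use. With only child age controlled, the second objective would report a mixture of these differences as an effect of nurse encouragement. Even a clean difference would show more or less engagement, not that professional involvement is necessary.

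The statement about effective online delivery has a related fault: nobody in the trial goes without the online program, so there is nothing to compare it with.

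**Working it through.** **1. What is randomised and what is claimed**

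| Element | Email prompts | Nurse recommendation |
|---|---|---|
| Assignment | Randomised 1:1 | By route of arrival, as reported by the parent |
| Source population | Same for both arms | One local government area versus Australia-wide |
| Infant age at invitation | Same for both arms | 2-week check versus up to 12 weeks |
| Primary outcome compared | Yes | Yes |
| Named control | Child age | Child age |
| Sample size calculation | Yes | None |
| Conclusion promised | Establish whether necessary | Establish whether necessary |

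The first three rows differ between the columns; the promised conclusion does not.

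**2. What is available for adjustment**

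Baseline questionnaire collects parent age, gender, education, employment, country of birth, language and household income, and infant birth order, among others. It also derives an area disadvantage index from postcode. The third objective will describe these characteristics by recruitment mode. Statistical methods compares demographics with Census data. Neither section says that they enter the comparison of outcomes by mode.

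**3. The plan's own sample size**

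Inputs (Sample size and condition allocation): SD 6.04, difference half an SD = 3.02 points, 80% power, p < 0.05 (taken as two-sided).

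n per arm = 2(1.96 + 0.842)² / 0.5² = 2 × 7.85 / 0.25 = 62.8, so 63 per arm and 126 in total, as stated. This covers the randomised arms only. No split by recruitment mode is given.

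**4. What an uncontrolled difference would do (illustration)**

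Assume 126 analysed, a two-sided t-test at 0.05, no true nurse effect, and a residual shift of b SD between recruitment groups. The chance of a significant result is about Φ(b√(n₁n₂/N) − 1.96). For b = 0.3 and 63:63, √(63 × 63/126) = 5.61, 0.3 × 5.61 = 1.68, and Φ(−0.28) ≈ 0.39. The t-based results are:

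| Assumed shift | In points (× 6.04) | 63:63 | 20% nurse-recruited |
|---|---|---|---|
| 0.1 SD | 0.60 | 9% | 7% |
| 0.2 SD | 1.21 | 20% | 15% |
| 0.3 SD | 1.81 | 39% | 27% |
| 0.5 SD | 3.02 | 80% | 61% |

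**5. Precision of the mode comparison (illustration)**

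Power for a true 0.5 SD difference between modes, N = 126, is about 80% at 50:50, 72% at 30:70, 61% at 20:80 and 39% at 10:90.

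Age adjustment costs some of this. Assume nurse recruits enrol evenly over 2–4 weeks and website recruits evenly over 2–12 weeks. Mean ages are then 3 and 7 weeks, and within-group variances are 2²/12 = 0.33 and 10²/12 = 8.33. With 20 nurse recruits of 126 (p = 0.159), the between-group variance is 0.159 × 0.841 × 4² = 2.14 and the within-group variance is 0.159 × 0.33 + 0.841 × 8.33 = 7.06. So r² = 2.14/9.20 = 0.23, |r| = 0.48, and the variance inflation is 1/(1 − 0.23) = 1.30. With 60 nurse recruits, |r| is about 0.69 and the inflation about 1.9. These figures describe precision, not confounding.

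**The case against.** - **The authors disclose the problem.** They do, and they chose the area to reduce it. What remains is that Statistical methods and the Discussion do not carry the caveat through.
- **Child age may be a minimum, with further covariates in an unseen analysis plan.** That is possible, and an article need not list every covariate. But the article fixes one control for all analyses, and no analysis plan can randomise recruitment mode or correct the wording of the Discussion.
- **Infant age, the most obvious difference, is controlled.** This stands if child age means age at enrolment. Region, socioeconomic position and self-selection remain.
- **The other baseline variables are used.** A reader might infer that they are collected and then ignored. The documents do not support that: the third objective describes them by recruitment mode. Only their use as covariates is unstated.
- **The rule for dual-exposed parents is reasoned.** A reader might infer that such parents are the most motivated and that the rule favours the nurse group. Nothing in the protocol shows this. The exposure of interest is nurse encouragement, and placing these parents in the website group would contaminate it. A sensitivity analysis is a reasonable check, not a correction of an error.
- **Remedies can cost more than they gain.** This stands. With 96 website recruits spread evenly over 2–12 weeks (assumed), restricting to 2–4 weeks would keep 96 × 2/10 ≈ 19. Many covariates with 20–40 nurse recruits could also be unstable. The adjustment set should be small.

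**Conclusion.** The point holds. As written, the plan would present a confounded, non-randomised contrast as a causal finding, and in the language of necessity. This rests on the text alone: what is randomised, the conceded group differences, the single named control, and the Discussion wording.

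The size of the bias is unknown. The probabilities, power and variance inflation above depend on an assumed recruitment split, assumed enrolment ages and an assumed residual shift, none of which the document gives. A reader might take the power and inflation figures as a measure of the confounding; they are not. Nor should a reader infer that the main trial result is compromised: the randomised email-prompt comparison is unaffected.

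The online-delivery statement in the Discussion is unsupported for a separate reason. Both arms receive the program, and the Background itself leaves efficacy to a larger later trial.

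**What to change.** 1. Label every nurse-versus-website comparison observational, and report it separately from the randomised email comparison.
2. Adjust it for infant age at enrolment and a small pre-specified set of variables already collected at baseline, for example education, income, area index, language and birth order. Keep the number in proportion to the nurse recruits obtained.
3. As optional sensitivity analyses, exclude dual-exposed parents and restrict website participants to Victorian postcodes. State the loss of precision with each.
4. Reword the Discussion and the Abstract to say that the trial will estimate the association of nurse recommendation with engagement. Remove the Discussion statement that the trial examines whether advice can be effectively delivered online.

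No new data are needed: the covariates and postcode are already collected. The cost is some analysis work, some loss of precision, and a weaker claim for the second objective.

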## Abbreviations

AHT: Abusive Head Trauma
FAS: Fatigue Assessment Scale
FSS: Fatigue Severity Scale
HREC: Human Research Ethics Committee
MCH: Maternal and Child Health
PND: postnatal depression
SSL: secure sockets layer
